**Methods/Design:**

The study population will consist of 270 acutely hospitalized patients referred for geriatric consultation at three sites. Paired assessments (live and online) will be conducted by independent, blinded geriatricians and the level of agreement examined. This will be compared with the level of agreement between two independent, blinded geriatricians each consulting with the patient in person (i.e. "live"). Agreement between the triage decision from live-live assessments and between the triage decision from live-online assessments will be calculated using kappa statistics. Agreement between the online and live detection of common geriatric syndromes will also be assessed using kappa statistics. Resource use data will be collected for online and live-live assessments to allow comparison between the two procedures.

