### Sample size and power analysis

The outcome of interest will be the difference in percentage agreement between paired assessments for live-live arm and online-live arm for the question: "is residential care recommended?", scored as "yes" (1) or "no" (2). A non-inferiority study tests whether the percentage agreement between clinicians in an intervention arm (online-live) does not lie beyond the lower limit of an acceptable range (a one-tailed area of clinical indifference) when compared with the standard clinical practice arm (live- live).

The sample size of 288 subjects (114 online-live, 114 live-live) was identified to provide the study with power exceeding 80% to detect a non-inferiority margin of 15% for levels of agreement between online-live when compared with live-live arms for the decision "yes, residential care is recommended". This is based on an assumption of inter-geriatrician agreement of 60% for geriatric triage decisions [8], allowing a two-sided type 1 error rate of 5%. With a 15% allowance for attrition, the adjusted sample size is 268 (i.e. 228/(1-0.15)). After rounding, 270 cases will be required in total between all sites.

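### The pre-attrition sample size is printed as 288, but the arm sizes and the attrition step use 228, and the power claim does not carry over to 228 unchanged

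*Protocol article*

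**What the plan says.** The section on sample size and power analysis opens its calculation with "The sample size of 288 subjects (114 online-live, 114 live-live"). To that total it attaches "power exceeding 80% to detect a non-inferiority margin of 15"%, an "assumption of inter-geriatrician agreement of 60% for geriatric triage decisions", and the words "allowing a two-sided type 1 error rate of 5"%. The attrition step comes next: "With a 15% allowance for attrition, the adjusted sample size is 268 (i.e. 228/(1-0.15")). The paragraph closes with "After rounding, 270 cases will be required in total between all sites". The abstract repeats the last figure: "The study population will consist of 270 acutely hospitalized patients".

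The Data analysis section makes the difference in agreement between the two groups the primary measure of reliability and the basis of the sample size.

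**The concern.** One phrase gives a total and two arm sizes that do not add up to it. The stated total before the attrition allowance (288) also exceeds the total after that allowance (268) and the enrolment target (270), which cannot be right for an inflation step.

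The misprinted number is the one to which the power claim for the primary comparison is attached. Someone checking recruitment or power against the article finds two benchmarks 60 subjects apart and cannot tell from the sentence alone which one the claim of more than 80% power describes. Changing the digit and leaving the rest of the sentence alone would attach that claim to 228 without anyone having checked it.

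**Working it through.** **Inputs.** All are from the section on sample size and power analysis unless noted.

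- Stated total 288; arms 114 and 114.
- Attrition 15%; adjusted total 268; final target 270 (the abstract also gives 270).
- Agreement 60%; margin 15 percentage points; type 1 error 5%, two-sided.
- Equal allocation. The Randomisation section randomises equally to four configurations, which under Study design are two orderings of the geriatricians within each of the two comparison arms. There is no third group to hold another 60 subjects.
- My assumption: true agreement is 60% in both arms. The article does not state the value for the online-live arm.

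**Step 1: the totals.**

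- Sum of arms: 114 + 114 = 228.
- Discrepancy: 288 − 228 = 60, and 60/228 = 26%.
- Attrition from 228: 228/(1 − 0.15) = 268.2. This reproduces the stated 268, then 270 after rounding.
- Reverse check: 270 × 0.85 = 229.5, which just covers 228.
- Attrition from 288: 288/0.85 = 338.8, which matches neither 268 nor 270.

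Only 228 fits the rest of the paragraph.

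**Step 2: the power that belongs to 114 per arm.** For non-inferiority with equal true agreement p, margin d and n per arm, the normal approximation is

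power = Φ(d/SE − z), with SE = √(2p(1 − p)/n).

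For n = 114: SE = √(2 × 0.6 × 0.4/114) = 0.0649, and 0.15/0.0649 = 2.31.

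- Two-sided 5% (one-sided 2.5%, z = 1.96): Φ(0.35) = 63.7%.
- One-sided 5% (z = 1.645): Φ(0.67) = 74.8%.

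For n = 144 (a total of 288): SE = √(0.48/144) = 0.0577, and 0.15/0.0577 = 2.60.

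- Two-sided 5%: Φ(0.64) = 73.8%.
- One-sided 5%: Φ(0.95) = 83.0%.

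| Per arm | Total | Two-sided 5% | One-sided 5% |
|---|---|---|---|
| 114 | 228 | 63.7% | 74.8% |
| 144 | 288 | 73.8% | 83.0% |

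The same formula needs 168 per arm (336 in total) for 80% power at two-sided 5%, and 132 per arm (264 in total) at one-sided 5%.

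**Step 3: other formulas the authors might have used.** Ordinary two-proportion comparisons (60% against 45% and 60% against 75%, one- and two-sided 5%, with and without continuity correction) need 240 to 372 in total for 80% power. Without the correction, 114 per arm gives 62.2% to 78.3% power. No variant tried exceeds 80% at 114 per arm.

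**The case against.** The strongest reply is that the paragraph corrects itself. The right arm sizes stand beside the wrong total, the attrition formula is written out with 228, and 268 and 270 follow. No arm size, enrolment figure or analysis depends on 288. This stands, and it limits the point to one wrong figure and the power claim tied to it.

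A reader might go further and infer that the trial needs 288 subjects and recruits only 270, so that it can never meet its own requirement, or that it should recruit 339. The document does not support this. That reading takes 288 at face value while ignoring the arm sizes and the inflation of 228 in the same paragraph.

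A second reply is that a power figure does not belong in the correction of a misprint, because it rests on choices the article does not fully fix. Part of this stands. Equal true agreement is my assumption, and the section speaks of a one-tailed region of indifference alongside a two-sided error rate, so a single figure of 64% without its conditions would claim too much. But the power claim is made about the number being corrected, so it has to be checked against the replacement, and it falls short at both error levels.

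A reader might also infer from the 83.0% at 144 per arm that 288 was the true output of the calculation and 228 the slip. That needs a one-sided 5% level, which is not the stated one, and it contradicts every other count in the paragraph. The article does not show what the original calculation returned.

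**Conclusion.** The point holds in a limited form. The pre-attrition total of 288 contradicts its own arm sizes and the attrition step by 60 subjects. It is most likely a digit slip for 228, and the target of 270 stands on 228. The arithmetic part rests on no assumption.

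The power part is conditional. Given 60% true agreement in both arms, a 15-point margin and a normal approximation, 114 per arm gives about 64% power at the stated two-sided 5% and about 75% at one-sided 5%. A different assumed agreement in the online-live arm would change these figures. On the inputs that are stated, the claim of more than 80% power should not be moved to 228 unchanged.

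**What to change.** Retrieve the original calculation and confirm which total it produced. If it confirms 228, replace 288 with 228 and state the power for 114 per arm, giving the assumed true agreement in each arm, the margin, the error level with its sidedness, and the method.

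This is slightly more than a change of one number, because the power statement has to be revised with it. The cost is a stated power likely to be less favourable than the present one. Arm sizes, the attrition allowance and the enrolment target of 270 need no change for this correction.

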### Data analysis

Agreement between the triage decisions from live-online assessments will be calculated using percentage agreement and kappa statistics, reported with 95% confidence intervals. This will also be calculated for the triage decisions from live-live assessments. Comparison of the difference in levels of agreement between the live-online group and the live-live group will be the primary measure of the reliability of the online assessment and is the basis for the sample size calculation for this project. Online assessment will be taken to be non-inferior to live assessment if percentage agreement in the live-online group is not more than 15% less than the percentage agreement in the live-live group.

The online assessment can be regarded in a similar manner to a diagnostic test, where the interest is in the number of patients recommended for a higher level of care from the online assessment compared with live assessment (i.e. false positives, specificity), and in the number of patients where important clinical diagnoses are missed in an online assessment (i.e. false negatives, sensitivity).

These measures will therefore be calculated and reported. Exploratory analyses of patient characteristics will be undertaken to examine these cases where differences of triage decision are identified. Agreement between the online and live detection of common geriatric syndromes will also be assessed using kappa statistics.

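### The planning inputs give about 64% power for the primary non-inferiority comparison, not the stated more than 80%

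*Protocol article*

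**What the plan says.** All the planning figures stand in the protocol article, under *Sample size and power analysis* and *Data analysis*.

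- **Outcome:** whether the two geriatricians in a pair agree on a yes/no question, namely whether residential care is recommended. The arms are compared on percentage agreement.
- **Margin:** online is accepted as non-inferior "if percentage agreement in the live-online group is not more than 15% less than the percentage agreement in the live-live group", so the 15% is a difference in percentage points.
- **Assumed agreement and error rate:** the calculation rests on an "assumption of inter-geriatrician agreement of 60% for geriatric triage decisions [8], allowing a two-sided type 1 error rate of 5" per cent.
- **Sample size:** "The sample size of 288 subjects (114 online-live, 114 live-live) was identified". The two arms add to 228, and the attrition step also uses 228 (228/0.85 = 268, rounded to 270). The printed 288 fits neither and is a separate slip.
- **Claimed result:** this size is said "to provide the study with power exceeding 80% to detect a non-inferiority margin of 15" per cent.

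The *Data analysis* section makes this comparison the primary measure of reliability and the basis of the sample size.

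**The concern.** With agreement at 60%, the variance of a binary outcome is close to its maximum, and 114 per arm looks small for a 15-point margin. The section gives every input that a power calculation needs, so the claim can be checked directly.

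The stake is how a negative result would be read. The trial asks whether online assessment is as reliable as live assessment. With power well below the stated figure, a method that is truly equivalent has a substantial chance of failing the test, and readers who trust the stated power would take that failure as evidence against the method.

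**Working it through.** **Inputs**

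| Input | Value | Source |
|---|---|---|
| Pairs per arm, n | 114 | *Sample size and power analysis* |
| Agreement, live-live | 0.60 | same section |
| Agreement, online-live | 0.60 | assumption: not stated; equal true agreement is the usual planning choice |
| Margin | 0.15 | *Data analysis* |
| Type 1 error | two-sided 5%, i.e. 2.5% in the non-inferiority direction | *Sample size and power analysis* |

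**Attempt to reproduce the stated power.** For two independent proportions with unpooled variance:

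- SE = √(2 × 0.6 × 0.4 / 114) = 0.0649
- margin / SE = 0.15 / 0.0649 = 2.312
- power = Φ(2.312 − 1.960) = Φ(0.352) = **63.7%**

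Exact binomial enumeration gives 63.6% when the test uses the Wald confidence limit and 64.9% when it uses the Newcombe limit. Using the variance under the null instead gives 62.3% to 63.2%. The shortfall is not caused by the approximation.

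**Sample size for 80% power.** n = (1.960 + 0.842)² × 0.48 / 0.0225 = 167.4, so 168 per arm and 336 pairs in total. With the plan's 15% attrition allowance, 336/0.85 gives 396.

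**Readings that might rescue the claim**

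| Reading | Power |
|---|---|
| One-sided 5%, 114 per arm: Φ(2.312 − 1.645) | 74.8% (132 per arm needed for 80%) |
| Two-sided 5%, all 270 evaluable (135 per arm) | 71.1% |
| Two-sided 5%, total of 288 (144 per arm) | 73.8% |
| Superiority formulas for 60% v 75% or 60% v 45%, 114 per arm, two-sided 5% | 62–68% |
| The same, one-sided 5% | 74–78% |
| One-sided 5% and 135 per arm | 80.8% |
| One-sided 5% and 144 per arm | 83.0% |

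Only the last two rows pass 80%. Each needs both a different error rate and a different n from those stated, and 135 per arm also needs no attrition at all.

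A rule that only checked whether the observed difference lay within 15 points would have 99.1% power, but it would wrongly accept a true 60% v 45% difference 52% of the time. It cannot be the basis of a 5% error rate.

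**What 114 per arm would fit.** Solving for 80% power at one-sided 2.5%: p(1 − p) = 0.0225 × 114 / (2 × 2.802²) = 0.163, so p = 0.794. At one-sided 5%, p(1 − p) = 0.207, so p = 0.71. With agreement kept at 60% and one-sided 2.5%, 80% would need a margin of 2.802 × √(0.48/114) = 0.182, about 18 points, or online-live agreement truly a little over 3 points better than live-live.

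**The case against.** The strongest reply is that the 60% may be the wrong figure, not the power. The article attaches it to geriatric triage decisions, which have several categories under *Data collection*, whereas the powered endpoint is a single yes/no question. Agreement after collapsing categories cannot be lower than before and is usually higher. At 80% agreement on the yes/no question, 114 per arm gives 80.8% power, which would match the claim. Printing 64% might then replace one wrong statement with another.

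This is a fair account of how the mismatch may have arisen, but it is inference. The section says that the size rests on 60%. If another value was used, the section misreports its input and still needs correcting. What stands is that the 64% is conditional on 60% agreement for the yes/no endpoint. That is why the correction should also give the agreement level at which 114 per arm reaches 80%.

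A second point is that the document does not give the true online-live agreement. Equality is the usual assumption, and the result is sensitive in both directions. A true online advantage of 3 points gives 79.8% power, while true online-live agreement of 58% gives 51% and 55% gives 33%. Nothing in the article suggests that an advantage was assumed.

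A third point also has merit: the words about one tail describe the region of clinical indifference, and the only error rate stated is two-sided 5%. The ambiguity in alpha is therefore minor, and the finding does not depend on it.

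**Conclusion.** The concern holds. With 114 evaluable pairs per arm, 60% agreement in both arms, a 15-point margin and two-sided 5%, power is about 64%, at least 16 points below the claim. A truly equivalent online method would fail to show non-inferiority about 36% of the time, where the plan implies less than 20%. No standard test at 114 per arm with a 5% error rate, one-sided or two-sided, reaches 80% on these inputs. At the stated error rate, neither 135 nor 144 per arm does so.

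The conclusion assumes equal true agreement in the two arms and takes the 60% as applying to the yes/no endpoint, as the section presents it. Because the error concerns the primary comparison, it must be corrected.

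**What to change.** In *Sample size and power analysis*:

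1. Replace the claim of more than 80% power with the delivered figure: about 64% with 114 evaluable pairs per arm and about 71% if all 270 patients complete, at one-sided 2.5% and 60% agreement in both arms.
2. Add that 114 per arm would give 80% power if agreement in both arms were about 79%. If the calculation in fact used a higher agreement for the yes/no question, state that value and its basis in place of the 60%, and give the power that follows from it.
3. State the error rate once, as one-sided 2.5%.

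The cost is a wording change and a less favourable stated power; no extra patients are needed. Rewording does not raise the power. If the sponsor wants 80% at 60% agreement, that takes 336 evaluable pairs, or 396 with the 15% attrition allowance.

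### On the plan's own inputs the non-inferiority floor for the yes/no item is 45% agreement, below the 50% of a coin toss, and no chance-corrected measure enters the success rule

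*Protocol article*

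**What the plan says.** In the protocol article, Sample size and power analysis defines the endpoint: "The outcome of interest will be the difference in percentage agreement between paired assessments for live-live arm and online-live arm", for a yes/no question on whether residential care is recommended. The margin appears in the power statement, "to detect a non-inferiority margin of 15% for levels of agreement between online-live when compared with live-live arms". On the reference level the section says "This is based on an assumption of inter-geriatrician agreement of 60% for geriatric triage decisions". Power is described as "power exceeding 80" per cent, "allowing a two-sided type 1 error rate of 5" per cent, with 114 pairs per arm.

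The success rule is in Data analysis: online assessment is non-inferior if "percentage agreement in the live-online group is not more than 15% less than the percentage agreement in the live-live group". That sentence contains no confidence limit, absolute floor or kappa condition.

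Kappa is planned. The abstract says that agreement "between the triage decision from live-online assessments will be calculated using kappa statistics", and Data analysis plans percentage agreement and kappa with 95% confidence intervals in both groups. It also plans sensitivity and specificity measures and an exploratory look at cases with differing triage decisions. None of these is tied to the non-inferiority claim.

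Data collection records the discharge recommendation in several categories: community, rehabilitation or geriatric unit, and permanent residential care at a high or low level.

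**The concern.** Raw agreement on a yes/no item has a high chance level. Two raters who both say yes in a proportion q of patients agree by chance in q² + (1-q)² of them, which is never below 50%. A 15-point margin below a 60% reference therefore reaches into the region where the online decision need not depend on the patient at all.

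The trial aims to show that online triage decisions are appropriate and reliable. If its success criterion can be met by a method that carries no information, meeting it does not support that claim. This follows from the margin and the measure, so a larger sample would not cure it.

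**Working it through.** **Inputs.** From Sample size and power analysis: yes/no item, live-live agreement 0.60, margin 0.15 on the difference in percentage agreement (read as absolute points), 114 per arm, two-sided 5%. From Data analysis: the success rule. The prevalence of a yes and the live-live kappa are not given, so values used below are assumptions.

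**The plan's own sample size.** n per arm = 2 × 0.60 × 0.40 × (1.96 + 0.84)² / 0.15² = 168, or 132 with a one-sided 5% level. Power at 114 is 63.7% or 74.8% respectively. The stated 114 does not reproduce. The attrition step does: 228/0.85 = 268.2. The sample size is a separate matter, and the steps below use 114 only as the stated number of pairs.

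**Implied floor.** 0.60 - 0.15 = 0.45.

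**Coin toss.** Agreement with a rater who says yes in a proportion q is 0.5q + 0.5(1-q) = 0.50 for every q. The true difference is 0.50 - 0.60 = -0.10, inside -0.15.

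**Kappa at these levels.** With equal yes-rates, kappa = (Po - Pe)/(1 - Pe), where Pe = q² + (1-q)².
- q = 0.5: Pe = 0.50. Kappa at 60% is 0.20 and at 45% is -0.10.
- q = 0.3: Pe = 0.58. Kappa at 60% is 0.05 and at 45% is -0.31.

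So 60% agreement corresponds to a live-live kappa of at most 0.20.

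**Probability that an uninformative method passes.** Exact binomial enumeration, 114 per arm. The point rule is observed difference ≥ -0.15. The CI rule is d - 1.96 × √[(pL(1-pL) + pO(1-pO))/114] > -0.15, where pL and pO are the observed live-live and online-live agreement and d = pO - pL.

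| Live-live agreement | Online method | Point rule | CI rule |
|---|---|---|---|
| 60% (plan) | coin, 50% | 0.79 | 0.12 |
| 65% | coin, 50% | 0.52 | 0.02 |
| 70% | coin, 50% | 0.23 | 0.003 |
| 83.2% (q = 0.3, kappa 0.6) | always no, 70% | 0.65 | 0.05 |
| 87.2% (q = 0.2, kappa 0.6) | always no, 80% | 0.95 | 0.36 |
| 92.8% (q = 0.1, kappa 0.6) | always no, 90% | >0.99 | 0.91 |

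In the last three rows live-live agreement is Pe + 0.6(1 - Pe), and always-no agreement is 1 - q. The lowest agreement and kappa that the margin accepts are:
- q = 0.2: 87.2 - 15 = 72.2%, kappa (0.722 - 0.68)/0.32 = 0.13.
- q = 0.1: 92.8 - 15 = 77.8%, kappa (0.778 - 0.82)/0.18 = -0.23.

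**Where the coin drops out.** The floor reaches 50% when live-live agreement is 0.50 + 0.15 = 65%.

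**The case against.** A reader might infer that the trial is set to declare a coin toss non-inferior whatever the data show. The documents do not support that, for three reasons.

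- **The 60% may not apply to the yes/no item.** It is described as agreement on triage decisions, which are recorded in several categories, and the success rule is also worded for triage decisions. With several categories chance agreement can be well below 50%, so 45% need not be below chance. Agreement on the yes/no item may well be higher, and at 70% a coin meets even the point rule only 23% of the time. This stands. It makes the mismatch between endpoint and assumption the likely root of the problem.
- **A confidence-limit test is probably intended.** The sample size section describes a test with a type 1 error rate, and 95% intervals are planned. On that reading a coin fails about 88% of the time even at 60%. This also stands for the pass rate. It does not move the coin outside the margin.
- **Other measures are reported.** Kappa, sensitivity and specificity would expose an uninformative method. That is a real safeguard for a careful reader, but the rule could be met while kappa sat near zero.

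Two smaller points. A relative reading of 15% gives a floor of 0.60 × 0.85 = 51%, just above a coin, but an endpoint defined as a difference in percentage agreement favours absolute points. The always-no figures rest on an assumed prevalence and kappa that the article does not give.

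**Conclusion.** The point holds in conditional form. On the article's stated inputs, with the margin in absolute points, the floor of 45% is 5 points below what a coin achieves, so an uninformative method counts as truly non-inferior. How often it would pass depends on the reading of the rule: 79% on observed percentages, 12% with a lower 95% limit.

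The coin-toss result rests on 60% being the agreement for the yes/no item, which is doubtful. A higher figure removes the coin but not the weakness. With an assumed live-live kappa of 0.6, always answering no still lies inside the margin at prevalences of 10% to 30%, and at 10% it passes even the CI rule 91% of the time. In either case the cause is that raw percentage agreement is the sole success criterion, with no correction for chance.

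**What to change.** 1. Replace the 60% with an agreement assumption that applies to the yes/no item, and state the floor that the 15-point margin then implies beside the agreement expected by chance.
2. Declare non-inferiority only if (a) the lower 95% limit of the agreement difference, online-live minus live-live, is above -15 points, and (b) the lower 95% limit of online-live kappa is above 0.
3. Report the difference in kappa between the arms with its confidence interval.

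Condition (b) is a minimum safeguard, not evidence of good agreement. It screens out always no, which has kappa 0, and nearly always a coin, whose expected kappa is 0. Kappa itself depends on prevalence, which is a reason to keep (a) beside it.

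The change needs no extra patients or data, since kappa with a 95% interval is already planned. The cost is that success becomes harder to claim. Simulated with 114 pairs and the large-sample standard error of kappa, (b) is met about 95% of the time or more at true kappa 0.4 to 0.6 and prevalence 20% to 30%. It is met about 78% of the time at kappa 0.4 and prevalence 10%. If online-live agreement really is 60%, so that kappa is at most 0.20, it is met at most about 58% of the time. That loss is substantial where the 60% is true, and the expected values should be settled before the rule is fixed.
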